### Health and educational outcomes based on the HPS framework

2.10

#### Academic performance

2.10.1

Study habits^[45]^ and grades were obtained to determine academic performance.^[46]^ A Study Habits Scale composed of 6 questions with a 5-point scale (completely false to completely true) explored students’ perceptions about their study habits.^[47]^ This instrument was translated and validated (Cronbach alpha = 0.74 and composite reliability = 0.70) for Brazilian adolescents.^[45]^ Additionally, mathematics and Portuguese language grades (ranging from 0 to 10 points) throughout of the year were requested from the Department of Municipal Education and/or provided by the Director of each school. The school- and grade-specific z-scores in Mathematics and Language will be used as academic performance variables.

#### Health-related quality of life (HRQoL)

2.10.2

The HRQoL self-report instrument (KIDSCREEN-27) for children and adolescents (from 8 and 18 years old) is a European measure with translation in several different languages, including Portuguese.^[48]^ A proxy measure to parents and caregivers also is available. The 27-item version was used in the current study, which covers the following dimensions: physical well-being, psychological well-being, autonomy and parent relation, peers and social support, and school environment. Students responded to questions about their PA and health (n = 5), general mood and feelings about themselves (n = 7), family and free time (n = 7), friends (n = 4), and school and learning (n = 4). Parents/caregivers also responded to these questions about their child, recalling the last week (i.e., how your child is, how does she/he fell, etc.).^[49]^

A Brazilian study demonstrated that KIDSCREEN-27 presented acceptable psychometric indicators of reproducibility (intraclass coefficient correlation = 0.70, 95% CI: 0.70–0.96), internal consistency (composite reliability index = 0.90, varied from 0.65 to 0.70 in the domains), and construct validity (confirmatory factor analysis = Factor loads were greater than 0.40, except for 5 items (0.28–0.39), and the model's goodness-of-fit indices were adequate) for adolescents from 10 to 15 years of age.^[50]^ In baseline, the KIDSCREEN-27 was completed by 921 adolescents (response rate of 92.2%).

#### Anthropometry

2.10.3

Adolescents’ body weight (kg), height (cm) (both used to calculate body mass index), and waist circumference (cm) were measured in a private room, by 45 minutes. Students were asked to take off shoes and wear light clothing. Body weight was measured once using a calibrated scale to the nearest 0.1 kg. A portable stadiometer (Altura exata brand) was used to measure height to the nearest 0.1 cm. Weight status was calculated based on the body mass index (BMI = kg/m^2^) by sex and age, based on the WHO cut-off points (http://www.who.int/growthref/en/, accessed on October 02, 2017). Waist measurement was taken at the narrowest point between the inferior rib border and the iliac crest, using an inelastic tape measure. Three measures of the circumference were recorded to the nearest 0.1 cm (if the discrepancy between the first 2 were lower than 1%, it was considered the average, otherwise, the median value of all the 3 measures was observed). All protocols were guided on international standardizations.^[51]^ Anthropometric measures were completed as follows: weight (n = 859; 86%); height (n = 861; 86%); and waist circumference (n = 861; 86%).

#### Physical fitness

2.10.4

Cardiorespiratory fitness (CRF) was assessed by the Progressive Aerobic Cardiovascular Endurance Run (PACER), a submaximal test adapted from the test of 20-m shuttle run.^[52]^ This test was validated for Brazilian adolescents, it is considered the best field test to measure CRF in adolescents.^[53,54]^

The test consists of 20-m shuttle run with a beep that indicates when the runner should reach or touch the demarcated ends. The initial speed is 8.5 km/h with a gradual increase of 0.5 km/h every minute. The test ends when the participant cannot reach the end twice before the beep. Different indicators will be analyzed as laps stages, minutes, and maximum oxygen consumption (VO_2_max) estimated by the Leger et al equation.^[52]^ The cardiorespiratory fitness test was administered to 779 students (intervention = 475 and control = 304) (response rate of 78%).

#### Other lifestyle variables

2.10.5

Self-reported frequency of consumption of fruit, vegetables, savory snacks, sweets, and sugar sweetened beverages in a typical week was assessed.^[15,24,37]^ The consumption of alcohol and tobacco on the last 30 days was also included.^[15,37]^ Sleep quality and duration on both weekdays and weekend days were self-reported.^[15,37]^ Body image was reported by self-assessment of 9 different silhouettes, each represented by a number (from 1—thinner to 9—fatter). The following questions were asked: which image is the best representation …of your physical appearance?... of a healthy body? …of the body you would like to have?.^[55]^

### Process evaluation

2.11

Protocol compliance (dose delivered and fidelity to each component) was determined during the intervention period using quantitative and qualitative methods. The quantitative evaluation was conducted by a previously validated instrument created for the *Movimente* Program, based on an evaluative matrix, taking into account the RE-AIM dimensions.^[56]^ The evaluation was conducted by the research team with data collected from students (during classroom time), teachers (at school), and parents (by telephone), over 3 stages, as described below.

#### Planning evaluation

2.11.1

A questionnaire was administered at baseline which aimed to explore the parents’ and teachers’ sociodemographic features; their interest in engaging in the program as well as perceived barriers and motivations to be part of the program. *Process evaluation:* A questionnaire was administered postintervention which aimed to explore the perception regarding the importance and quality of the strategies, their engagement (teachers only) as well as perceived barriers and facilitators (teachers and parents only), and, finally, their intentions to continue being part of the program (teachers only).

Interviews were also conducted with teachers and coordinators to gain a deeper understanding of their perceptions of the program. They were interviewed one-on-one and perceptions, opinions, and barriers to implementation of the program were discussed. The interviews were conducted using a semistructured interview-guide during school time, lasting approximately 15 minutes. Conversations were recorded and consent was given after transcription.

### Data treatment and statistical analyses

2.12

The tabulation of questionnaire data will be performed using an optical reading using the software “SPHYNX.”^[57]^ At the end of the process, the tabulation will be manually checked by 2 staff members of the Movimente study team. The management and processing of the database as well as the descriptive analyses will be performed in the statistical package “STATA Standard Edition 15.”^[58]^ Inferential analyses will be performed in both STATA and R Project for Statistical Computing 3.5.1 software.^[59]^

Descriptive analyses will be performed to describe the sample, presenting mean values for continuous variables and absolute and relative frequency for qualitative variables, both with their respective 95% confidence intervals (95% CI). Pearson *χ*^2^ tests will be used to compare sociodemographic characteristics among adolescents with valid PA accelerometer data to those without valid data.

The multilevel approach for repeated measurements will be applied through the application of generalized linear mixed models in the inferential analyses of PA and SB (primary outcomes). The models will be tested in relation to their assumptions of normality and independence of residues, as well as checked in relation to homoscedasticity. If these assumptions are not met, linear models for different families (e.g., Gamma) will be tested that are better suited to the features of the modeled variables. Transformation of non-normally distributed variables will be performed where appropriate. In addition, Akaike information criterion (AIC), and Bayesian information criterion (BIC) will be applied to evaluate models fit.

Regarding mediation, the following steps will be followed: action theory test (Pathway A: to investigate the impact of the intervention on hypothesized mediators at time 2, controlled for baseline values); conceptual theory test (Pathway B: to analyze the association between mediators and the dependent variable at time 2, controlled for group assignment and baseline values); to verify the total effect (Pathway C), direct effect (Pathway C’: analyze the effect of the intervention that is not explained by the mediators) and indirect effect (Pathway AB: the mediated effect) of the intervention for each outcome; a significance test of the mediated effect and the proportion mediated [AB/ (C’ +AB)] were calculated. Then, a multiple mediator model will be performed by including the significant mediators.^[60]^

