### Power calculation

2.2

All sample size power calculations considered a statistical power of 80% and a 5% significance level for 2-tailed tests. An odds ratio of 2^[18]^ was considered meaningful, that is, students from the intervention group would be 2 times more likely to become active (self-report measure) compared with their peers from the control group. Considering these parameters and the sample design (RCT), a minimum sample of 517 subjects (1:1 between intervention and control groups) was estimated using the software OpenEpi.^[19]^ Because of the clustered nature of the sampling frame,^[18]^ the study sample was doubled to n = 1034 schoolchildren.

When estimating a sample size for PA as a continuous variable (self-report measure) using the software GPower 3.1, a sample of 1090 students has a statistical power to identify effect size equal to or higher than 0.17 (i.e., intervention vs control differences of 200 minutes per week in PA, the primary outcome) in scores in the adjusted comparisons between control (intervention and control) versus time (baseline and follow-up), considering the effect size found in a previous study using subjective measures.

Finally, considering the sample power for mediation analyses procedures (based on a simulation study from Fritz and MacKinnon ^[20]^), the needed sample to detect small mediation effects (standardized change of 0.14 or higher) when testing the mediating role of variables (i.e., social support for PA) in the intervention effect on primary outcomes is 539 for mediation analyses using PRODCLIN and 462 subjects for Bias-corrected bootstrap methods.^[20]^

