### Recruitment of schools and participants

2.4

The study was approved by the Municipal Secretary of Education, Florianopolis and recruitment of schools occurred from October to November 2015. An invitation was sent to the 18 schools by email, asking the principal of each school if they were interested in being part of the *Movimente*, irrespective of the study condition (intervention or control). Out of 18 schools, 7 agreed to participate in the research. One school (n = 6 classes) was selected for conducting the pilot study, and 6 schools were matched (number of classes and geographic location) and randomly assigned to intervention or control arms. This matched process was adopted to avoid contamination between groups (intervention and control) and guarantee an equal distribution of schools from different geographic areas in both the groups. Also, we matched schools considering the sample size (based on the number of classes) because it varied greatly between schools (from 7 to 13 classes). The socioeconomic backgrounds and teaching schedules of these schools are the same. They were all municipal public schools, with a target audience that is very similar in terms of economic and human development index. Thus, the allocations were made to get a peer-grouped (1:1 ratio) aimed to achieve a balance between trial levels (3 schools in intervention group and 3 in control group), considering the number of classes in the schools (2 schools had between 6 and 8 classes; and 4 schools had between 9 and 11 classes).

To avoid contamination between control and intervention groups, schools were not informed about which group they were in until after baseline data collection. All students in grades 7 to 9 from the 6 selected schools who attended the first weeks of school (1427 students) were eligible to be part of the program (intervention = 796 and control group = 631). In baseline data collection, a total of 370 parents did not deliver their consent after 5 attempts to send the consent form for their children and a telephone call attempt. Fifty-eight students declined to be part of the research, and 999 adolescents (response rate = 70%) completed the baseline questionnaire (intervention group n = 580; response rate = 72.9%; control group: n = 419; response rate: 66.4%). Adolescents with mental and/or physical disabilities as well as those who did not attend the first 3 weeks of the school year (period of the collecting data) were not eligible.

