#### General teachers

2.6.4

Classroom teachers from grades 7 to 9 from the intervention schools were invited to take part in the training session, which was organized in 3 stages. The first session was a 4-hour face-to-face meeting. To reach these teachers, different training days were offered. Those who agreed were enrolled in a session at school to discuss health (e.g., definition, relevance, among other topics) and its influence on all aspects of students’ life such as their behavior during classes, concentration, study habits, and academic performance.

A supplementary handbook was provided aimed at assisting teachers with several lessons plans regarding health concepts. The material was presented to teachers and its content was discussed to demonstrate several possibilities of activities to be conducted in the classroom, in different subjects. This material was adapted from a previous work,^[15]^ elaborated by the research team during monthly meetings over a year (2014/2015), taking into account either the National Curriculum Standards and the cultural aspects from Florianopolis, Santa Catarina. The handbook was divided into several sections: introduction; purpose and methodology; breaks activities guide; and 1 chapter for each of the school disciplines (e.g., Maths, Portuguese). Thus, sessions were provided by 8 activities suitable for each discipline, which were structured as follows: purpose, required material, development and suggestions to adapt the activity, and complementary text.

The session regarding breaks activities guide consisted of concepts, aims, and examples of: relaxation and stretching breaks; muscle activation breaks; and energizers breaks. Teachers were informed that the material was flexible. In other words, they could adapt the lesson content to suit the needs and abilities of their class.

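### The only stated response to a failed independence check in the primary mixed models is a new distribution family, which cannot remove residual correlation

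*Protocol article*

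**What the plan says.** Section 2.12 (Data treatment and statistical analyses) analyses PA and SB, the primary outcomes, with generalized linear mixed models in a multilevel, repeated-measures framework. It then sets out the diagnostics: "The models will be tested in relation to their assumptions of normality and independence of residues", with homoscedasticity checked as well. The next sentence gives the consequence of failure: "If these assumptions are not met, linear models for different families (e.g., Gamma) will be tested". It covers all three assumptions together and names no other response.

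Two neighbouring sentences matter. Transformation is mentioned separately and only for variables that are not normally distributed, so it is not offered for failed independence. AIC and BIC are to be used to evaluate model fit, with no instruction to revise the correlation structure.

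Three features of the design bear on dependence:

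- Section 2.4 describes six schools, three per arm, and their size: "2 schools had between 6 and 8 classes; and 4 schools had between 9 and 11 classes".
- Section 2.6.4 tells teachers in the intervention schools that "they could adapt the lesson content to suit the needs and abilities of their class".
- Section 2.7.2 measures students at three time points: T0, T1 and T2.

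**The concern.** The rule has three triggers and one remedy, and the remedy suits only two of them. Moving from a normal to a Gamma model changes the assumed shape and the mean-variance relation. It does not alter which observations the model treats as conditionally independent. If the diagnostic finds that residuals move together within a class, a school or a student, refitting with another family and the same random effects leaves that dependence where it was.

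Dependence beyond the random effects is plausible here. Lessons are delivered and adapted class by class, other components act on whole schools, and students are measured repeatedly. What is at stake is the standard error of the intervention-by-time effect on the primary outcomes, in exactly the case where the plan's own check has flagged a problem.

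**Working it through.** **Reference level.** Section 2.2 states: "All sample size power calculations considered a statistical power of 80% and a 5% significance level for 2-tailed tests". Its continuous-outcome figure reproduces. With effect size 0.17, n per arm = 2 × (1.96 + 0.8416)² / 0.17² = 543.2, so 544 per arm and 1088 in total; the t-test version gives 1090, as stated. The benchmark is therefore a two-sided 5% test. The article gives no intraclass or residual correlation, so every correlation below is an assumption.

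**Step 1: why intercepts alone do not protect the contrast.** Write the outcome as fixed effects + student intercept + school intercept + residual. The intervention effect is a between-arm difference in change from T0. Intercepts that are constant over time cancel from a change. A component of change shared by a class therefore stays in the residual unless a time-varying class or school term is present. As a check, a student random-intercept model fitted to two balanced waves gave the same standard error for group-by-time as ordinary least squares on change scores (0.08800 in both). Intercepts-only is an assumption, because the article does not list the random effects.

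**Step 2: class-shared change, by formula.** From section 2.4, the number of classes lies between 2×6 + 4×9 = 48 and 2×8 + 4×11 = 60. (The same section also mentions 7 to 13 classes per school; the point does not depend on which is used.) With 999 students, the mean class size is m = 999/60 = 16.65 to 999/48 = 20.81, and 18.5 at 54 classes. Let ρ be the share of change variance common to a class and not captured by any term. Then DE = 1 + (m − 1)ρ, and the false-positive rate is 2 × [1 − Φ(1.96/√DE)].

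| Classes | m | ρ = 0.02: DE, rate | ρ = 0.05: DE, rate |
|---|---|---|---|
| 48 | 20.81 | 1.396, 9.7% | 1.991, 16.5% |
| 54 | 18.50 | 1.350, 9.2% | 1.875, 15.2% |
| 60 | 16.65 | 1.313, 8.7% | 1.782, 14.2% |

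**Step 3: the same by simulation.** The setting was 54 classes of 18 in six schools, with student and school intercepts present, analysed within student over 4000 runs. Class-by-wave shares of within-student variance were 0 / 0.02 / 0.05.

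- Two waves: 5.0% / 9.3% / 15.4%.
- Three waves, T1−T0: 5.0% / 9.3% / 15.5%.
- Three waves, T2−T0: 4.8% / 9.6% / 15.3%.

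A further run that ignored the class gave 9.7% / 15.8% at 0.02 / 0.05, and 5.3-5.8% when class or school means were compared. Another, ignoring all clustering in change scores, gave 7.9% / 14.6%. Comparing six school means (t, 4 df) in that setting gave 4.6% / 4.5%.

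**Step 4: leftover serial correlation only.** Suppose a student random intercept is fitted but the residuals follow AR(1) with correlation r over three equally spaced waves. The model's implied contrast variance is 2 × [1 − (2r + r²)/3]. The true variance is 2(1 − r) for T1−T0 and 2(1 − r²) for T2−T0.

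| r | Model | True T1−T0, rate | True T2−T0, rate |
|---|---|---|---|
| 0.2 | 1.707 | 1.60, 4.3% | 1.92, 6.5% |
| 0.4 | 1.360 | 1.20, 3.7% | 1.68, 7.8% |
| 0.6 | 0.960 | 0.80, 3.2% | 1.28, 9.0% |

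The T1 contrast becomes conservative and the T2 contrast too liberal.

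**The case against.** The strongest reply is that the plan already handles correlation through the model. Section 2.12 specifies mixed models, whose random effects are there to absorb dependence within students and schools. Nothing says they are dropped when the family changes; a Gamma mixed model can keep them. The families are also described as those better suited to the variables, which reads as being about shape, so the authors may never have meant a new family to answer failed independence. The random-effects and covariance structure is commonly left to a full protocol or analysis plan, which is not shown here, and its absence is no finding.

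Most of this stands, and it limits the point. A reader might infer that correlated residuals will remain in the primary models and that false positives will exceed 5%. The article does not support that. The rule acts only if the check fails after the random effects. The percentages rest on assumed correlations and on a model with no term for shared change. If school-level variation in change is modelled, class correlation is largely absorbed, as the six-school comparison in Step 3 shows. Serial correlation alone makes T1−T0 conservative. A reader might also take transformation to be a proposed cure for dependence, but the text ties it to non-normality.

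What the reply does not remove is the rule itself. When the independence check has failed, the planned random effects have by definition proved insufficient, and the same random effects under another family leave the same gap. AIC and BIC do not direct the analyst to the correlation structure. This is a stated instruction that is wrong for one of its three triggers, not a detail left for later.

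**Conclusion.** The point holds in conditional form. Section 2.12 attaches to failed independence a remedy that cannot work. If the check fails after the planned random effects and the rule is applied literally, residual correlation persists and the standard errors of the intervention-by-time effect on PA and SB can be wrong.

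For scale, an uncaptured class-shared part of the change of 2% or 5% gives false-positive rates of roughly 9-10% or 15-16% at a nominal 5%. This assumes 48 to 60 classes, about 999 students and no time-varying class or school term. Leftover serial correlation of 0.2 to 0.6 gives 3.2-4.3% for T1−T0 and 6.5-9.0% for T2−T0. None of these correlations comes from the article, so the figures illustrate the risk and do not predict this trial's error rate.

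**What to change.** Split the rule in section 2.12 into two.

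- **Non-normality or unequal variance:** use another distribution family or a transformation, as now planned.
- **Failed independence:** revise the correlation structure. Options are school-by-time terms, class-level terms that allow for shared change, or a within-student covariance across T0, T1 and T2.

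Two details need fixing with it. Class should be defined as the class at baseline, because T2 falls in the following school year and classes may not stay the same. School-level inference should use small-sample methods, because ordinary clustered standard errors are unreliable with six schools.

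The cost is a sentence or two in the analysis section and one or two extra variance terms if the check fails. The downside is somewhat wider confidence intervals.
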